### Statistical analysis plan

#### General analysis principles

The code of the database will not be broken until all efficacy and safety data up to the last patient are included in the database, after data verification and validation are performed, and after the SAP has been accepted for publication. Analysis will be performed by the investigators of the PASS study group (see Acknowledgements section) assisted by a biostatistician of the Academic Medical Centre in Amsterdam.

#### Patient flow diagram

The flow of participants will be displayed in the Consolidated Standards of Reporting Trials (CONSORT) Flow diagram (Figure 
1). Due to the pragmatic design of the study, the total number patients assessed for eligibility has not been assessed.

**Figure 1 Fig1:**
[figure not shown]
**Flow-chart of patients.**

### Definition of intention-to-treat and per-protocol population

Main analysis will be performed according to the intention to treat (ITT) principle. The safety analysis will be performed in a per protocol (PP) analysis. If a patient was by fault randomized more than once, the first randomization outcome was used. Patients who withdrew consent directly after randomization (that is, before treatment was initiated in those randomized for ceftriaxone in addition to standard care, or within 6 hours after randomization in those randomized for standard care) will be excluded from analysis. Patients with protocol deviations in eligibility are included in the ITT analysis and will be tabulated (Table 
1). Patients not receiving their allocated treatment due to instantaneous crossover are considered protocol violations; these patients will be included in the ITT population. PP analysis will exclude patients for whom protocol deviations in treatment and eligibility were made (see protocol deviations in eligibility and protocol deviations in treatment).

**Table 1 Tab1:** **Number and type of protocol violations in eligibility**

Type of protocol violation in eligibility	Ceftriaxone + standard care (n = …)	Standard care (n = …)
Age <18 years		
Stroke		
No neurological symptoms (NIHSS = 0)		
Onset of stroke >24 hours ago		
Admission		
Infection at admission		
Use of antibiotics <24 hours before admission		
Pregnancy		
Known hypersensitivity to cephalosporins		
Previous anaphylaxis for penicillin derivates		
Subarachnoidal hemorrhage		
Death is imminent		
Total number of protocol violations in eligibility		

### Handling of missing data

If outcome data could not be obtained at the 3 month evaluation, we will first check the municipal council to ensure that the patient is not deceased. All other patients are considered lost to follow-up and will be tabulated, including the percentage of missing outcome data and the association with treatment. Missing outcome data will be obtained by imputation, using the coefficients of five rounds of imputation to obtain the final estimates. We will perform sensitivity analysis. First, we will use single imputation by last observation carried forward (LOCF). An observer blinded for treatment allocation will obtain the last observational score on the mRS using the medical charts and the letters of discharge of the stroke episode. All patients with LOCF will be tabulated with an explanation for the loss to follow-up (Table 
2).

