### Summary study protocol

PASS is a multicenter prospective, randomized, phase III, open-label, blinded end-point superiority trial (PROBE) of standard care with preventive ceftriaxone treatment compared to standard care without preventive ceftriaxone. Adult patients with stroke (both ischemic and hemorrhagic), a score ≥1 on the National Institutes of Health Stroke Scale (NIHSS) and stroke onset within 24 hours were included
[8]. Patients were excluded in case of infection at admission, use of antibiotics within 24 hours before admission, previous hypersensitivity or anaphylaxis to cephalosporins or penicillin, subarachnoid hemorrhage, pregnancy or when death seemed imminent. Patients were randomly assigned to either ceftriaxone at a dose of 2 g, given every 24 h intravenously for 4 days, in addition to stroke-unit care, or standard stroke-unit care without preventive antibiotic therapy. Randomization was performed through ALEA (online software for randomized trials;
https://nl.tenalea.net/amc/ALEA/Login.aspx) and is based on a uniform distribution; weight of the arms is equal (1:1). Randomization is stratified according to study center (academic hospital, large non-academic hospital, or small non-academic hospital) and stroke severity (score on NIHSS 1 to 9 or >9) and performed by using random blocks with a maximum block size of 6; blocks of 2, 4 and 6 are made per stratum combination

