[9]. The study has a PROBE design, which implies that blinding is lost, but only as to treatment. Patient and physician were aware of treatment allocation; however, the assessors of outcome were not. Data were collected on admission, during hospital stay, and at 3 months by standardized case record forms. The primary outcome is functional outcome at 3 months follow-up, as assessed on the mRS during a structured telephone interview by a trained assessor blinded for treatment allocation. Secondary outcomes are death rate at discharge and at 3 months, infection rate during hospital admission, length of hospital admission, volume of post-stroke care, use of antibiotics during hospital stay, quality adjusted life years (QALYs) and costs. Safety outcomes are complications of treatment, Serious adverse events (SAEs) and suspected unexpected serious adverse reactions (SUSARs). In the initial trial protocol, we presented a binary logistic regression analysis on the dichotomized mRS (0 to 2 versus 3 to 6) as primary outcome, requiring a sample size of 3,200 patients, and a proportional odds model in a secondary analysis of the primary end point
[9]. Blinded for any of the outcomes, we have changed the primary analysis in PASS from a binary logistic to an ordinal logistic regression on the original mRS, enhancing statistical power. The adapted power analysis showed that with identical assumptions on the clinical effect, using a 0.05 two-sided significance level and 80% study power, 2,550 patients were needed
[9]. The analysis of dichotomized mRS data will now be the secondary analysis of the primary end point.

On 23 March 2014, all patients were included and the last follow-up is expected in June 2014. For the complete study protocol and update, we refer to previous publications
[6, 7].

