### Protocol developments

PASS is registered at current controlled trials (
http://www.controlled-trials.com; ISRCTN: 66140176; date of registration: 6 April 2010). The medical-ethical board of the Academic Medical Center, Amsterdam, approved the protocol on 5 May 2010, and 29 Dutch participating centers were added in the course of the study. Due to the change in primary analysis of primary outcome from a binary logistic approach to an ordinal logistic regression analysis and an expected rate of patients lost to follow-up and/or patients with incomplete data of 5%, the total sample size was reduced from 3,200 patients to 2,550 patients in 2014
[7]. Importantly, no changes were made regarding the primary outcome measurement (that is, the assumed size of the effect on the mRS). This update of the protocol was recently published in this journal
[7].

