### Analysis of primary outcome

An ordinal regression model on the total range of the mRS will be performed as the first analysis of primary outcome, under the assumption of proportional odds
[7]. The distribution of primary outcome (for example, functional outcome on the mRS) in both treatment groups will be expressed in a histogram (Figure 
4). Both adjusted and unadjusted analyses will be performed and reported. In clinical trials, adjusting for prognostic covariates improves statistical power, can correct for imbalances in baseline prognostic variables and can reduce variability in data
[17, 18]. The choice of prognostic covariates is mostly based on imbalances across treatment groups, prognostic factors that are related to the primary outcome, or a combination of both
[17]. As the investigators are blinded for all outcome data until the statistical analysis plan is accepted for publication, we chose to use the most important prognostic factors for outcome after stroke: age, stroke severity on the NIHSS, history of stroke, history of diabetes, prior disability as defined on mRS, and stroke type
[19]. Stratification of randomization was performed according to both study center and stroke severity, so we will also include study center as a covariate. The second analysis of the primary endpoint, that is, the dichotomized score on the mRS (for example, favorable versus unfavorable, mRS 0 to 2 versus mRS 3 to 6), will be expressed as OR with 95% confidence intervals (CI; Table 
4). Results of the dichotomized approach will be compared to the results of the primary analysis of primary outcome.

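### Missing 3-month mRS is imputed only five times with no seed stated, so a primary P-value close to 0.05 would depend on the random seed

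*SAP article*

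**What the plan says.** The SAP article, Handling of missing data, states for patients whose 3-month mRS cannot be obtained: "Missing outcome data will be obtained by imputation, using the coefficients of five rounds of imputation to obtain the final estimates". It then introduces sensitivity analyses: last observation carried forward from charts and discharge letters, and a joint model of loss to follow-up and mRS. The five-round imputation is therefore the main method.

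It feeds the primary analysis, for which the article plans: "An ordinal regression model on the total range of the mRS will be performed as the first analysis of primary outcome" (section Analysis of primary outcome). The design figures, given in Summary study protocol, are "using a 0.05 two-sided significance level and 80% study power, 2,550 patients were needed". Under Protocol developments, the reduced sample size allows for "an expected rate of patients lost to follow-up and/or patients with incomplete data of 5" per cent.

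The article gives no seed and does not say how standard errors are combined over the five rounds.

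**The concern.** Each round of imputation draws the missing scores at random. The pooled estimate therefore carries a Monte Carlo error that comes from the random-number seed and shrinks only as the number of rounds grows. With five rounds this error is small relative to the standard error, but it is not negligible when the test statistic lies near the critical value. The analysis concerned is the primary test at two-sided 0.05. In a borderline trial, two analysts who both followed the text could report P-values on opposite sides of the threshold from the same data. Changing the number of rounds or choosing a seed after the code is broken would look post hoc.

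There is a smaller point of wording. The sentence mentions coefficients but not variances, so a reader cannot tell from it that the between-imputation variance will enter the confidence interval.

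**Working it through.** **Inputs from the SAP article.** Imputations m = 5 (Handling of missing data). Two-sided alpha 0.05, power 80%, N = 2,550 (Summary study protocol). Expected lost or incomplete 5%, which is 0.05 × 2,550 = 127.5, about 128 patients (Protocol developments). The article gives no figure for Monte Carlo error, so there is none to reproduce. The 2,550 itself cannot be re-derived because the article gives neither the effect size nor the mRS distribution. The calculation below does not need them.

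**Assumption.** The fraction of missing information, g, is not in the article. I take 5% as the reference, equal to the expected loss, and show 1%, 2% and 10% as a range.

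**Seed error of the test statistic.** Scale the total variance with unlimited imputations to 1, so that the within-imputation variance is W = 1 − g and the between-imputation variance is B = g. Near the threshold, the seed-to-seed SD of z is approximately √(B/m). For g = 0.05 and m = 5 this is √(0.05/5) = 0.10. If the long-run z is 1.96, 95% of seeds give z between 1.96 − 1.96 × 0.10 = 1.764 and 1.96 + 1.96 × 0.10 = 2.156. The corresponding P-values are 0.078 and 0.031.

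95% seed range of P when the long-run P is 0.05:

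| g | m = 5 | m = 50 | m = 100 |
|---|---|---|---|
| 1% | 0.041–0.061 | 0.047–0.053 | 0.048–0.052 |
| 2% | 0.037–0.066 | 0.046–0.055 | 0.047–0.053 |
| 5% | 0.031–0.078 | 0.043–0.058 | 0.045–0.055 |
| 10% | 0.025–0.092 | 0.041–0.061 | 0.043–0.058 |

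**Simulation check.** One trial of 2,550 was simulated in each of two settings, with an assumed mRS distribution, about 5% of scores missing at random (121 and 134 patients) and proportional-odds imputation. In each, 100 imputations were resampled in sets of five, pooled by Rubin's rules and centred at z = 1.96. Estimated g was 0.050 without and 0.049 with a prognostic covariate. The SD of z was 0.102 in both. The P range was 0.031–0.078 and 0.031–0.080.

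**How often it would matter.** With 80% power the mean of z is 1.96 + 0.84 = 2.80. The chance that two seeds fall on opposite sides of 1.96 is about φ(0.84) × 2σ/√π, where σ is the seed SD and φ(0.84) = 0.280. At g = 5%:

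- m = 5: 0.280 × 2 × 0.10/1.772 = 0.032, about 3% of trials.
- m = 100 (σ = √(0.05/100) = 0.022): 0.280 × 2 × 0.022/1.772 = 0.007.
- m = 5 with no treatment effect (both tails, φ(1.96) = 0.0584): 2 × 0.0584 × 2 × 0.10/1.772 = 0.013.

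**Efficiency.** Relative to unlimited imputations, 1/(1 + g/m) = 1/(1 + 0.05/5) = 0.990.

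**If variances were not combined.** Rubin's total is T = W + (1 + 1/m)B = 0.95 + 1.2 × 0.05 = 1.01. Using W alone makes the standard error √(0.95/1.01) = 0.970 of the correct one. The actual type I error is then 2 × [1 − Φ(1.96 × 0.970)] = 0.057. The same calculation gives 0.994 and 0.051 at g = 1%, 0.988 and 0.053 at 2%, and 0.939 and 0.066 at 10%.

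**The case against.** The best defence is that five imputations are statistically sound. Rubin's total variance contains the term B/m, so the finite number of draws is already paid for. The estimate is not biased and the type I error is not inflated. The loss of efficiency is about 1%. This stands, and a reader should not infer that the planned primary analysis is invalid.

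A reader might also infer from the sentence that only coefficients are pooled and that the confidence interval will be too narrow. The article does not say so. It contains no word that excludes variances, it is a condensed account, a biostatistician assists with the analysis, and Rubin's rules may well be intended. The standard-error figures therefore describe a possible misreading and not a stated plan. For the same reason, the lack of a seed in an article is not itself an error. The number five, however, is a stated choice.

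A reader might further infer that opposite verdicts are likely. They are not: about 3% of trials under the planned effect and about 1% under no effect, at 5% missing information.

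Finally, 5% is probably too high for missing mRS. The article's figure also covers incomplete data, and deaths are traced through the municipal register, which leaves fewer scores to impute. In-hospital data could lower the missing information further. This is fair and shrinks the effect, but even at 1% the range of P still straddles 0.05. The planned sensitivity analyses do not remove the seed error from the primary result.

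**Conclusion.** The point holds as one of reproducibility. With five imputations and no stated seed, a primary P-value near 0.05 is settled partly by the seed: about 0.031 to 0.078 for a long-run P of 0.05 if missing information is 5%, and less if it is lower. It has no practical effect on a result well away from the threshold. The size rests on the assumed fraction of missing information; the simulation also assumes an mRS distribution and scores missing at random. The pooling of variances is a matter for clarification, with a worst case of a 3% understatement of the standard error and a type I error of about 5.7% at 5% missing information. It is worth changing because the remedy is almost free and can be made credibly only before the code is broken.

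**What to change.** In Handling of missing data, replace the five rounds by a stated number between 50 and 100 and give a seed fixed before the code is broken. In the same sentence, say that the coefficients and their variances are both combined by Rubin's rules. At 5% missing information this narrows the seed range of a long-run P of 0.05 to about 0.043–0.058 with 50 imputations, or 0.045–0.055 with 100. A fixed seed makes the reported figure repeatable. The cost is one revised sentence and extra computing time, with no additional patients or data.

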**Table 2 Tab2:** **Assessment of follow-up by LOCF according to treatment allocation**

**Patient number**	**Explanation**	**Treatment allocation**

We will also perform a sensitivity analysis of baseline characteristics of the group of patients not lost-to-follow-up versus all patients included in PASS. In addition, we will also perform a joint model analysis of the loss to follow-up and the mRS change during follow-up
[10]. Missing values of baseline characteristics will not be included or imputed in the display of baseline characteristics. When values are missing for dichotomous variables, the actual denominator will be stated. In case of continuous variables, a footnote will be added to show the number of patients for whom the variable was missing.

### Protocol deviations in eligibility, consent procedure, treatment

When a patient was randomized but did not adhere to inclusion or exclusion criteria, this was considered a protocol deviation regarding eligibility. Patients with protocol deviations in eligibility were included in the ITT analysis, but excluded from PP analysis.In each center, the local investigator obtained written informed consent from the patient or representative according to the PASS study protocol. Patients who withdrew consent directly after randomization were excluded from further analysis. The flow of patients is displayed in the CONSORT flowchart (Figure 
1).

Treatment allocation was regarded as carried out according to the study protocol when a patient randomized for ceftriaxone in addition to standard care received ceftriaxone 2 gram each 24 hours for 4 days. Patients were also considered as treated PP when treatment was terminated within 4 days due to discharge, death, a palliative care policy, an allergic reaction without anaphylaxis or a previous allergic reaction in medical history (see inclusion and exclusion criteria and protocol deviation in eligibility), other side effects of treatment, or when treatment with ceftriaxone was changed into treatment with another antibiotic because of an infection because these situations and what to do were all defined and described in the initial protocol
[6]. In patients allocated to standard care, treatment was carried out according to the study protocol when patients did not receive preventive antibiotic therapy.

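### The SAP limits the safety tables to the per-protocol set, so some patients who received preventive ceftriaxone leave them together with any harm they had

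*SAP article*

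**What the plan says.** The SAP section on the intention-to-treat (ITT) and per-protocol (PP) populations states: "The safety analysis will be performed in a per protocol (PP) analysis". It adds that "PP analysis will exclude patients for whom protocol deviations in treatment and eligibility were made". The section on protocol deviations repeats this for eligibility: "Patients with protocol deviations in eligibility were included in the ITT analysis, but excluded from PP analysis". The two sections on safety outcomes and Tables 5 and 6 name no other population.

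Table 1 has two allergy rows among the eligibility violations: "Known hypersensitivity to cephalosporins" and "Previous anaphylaxis for penicillin derivates".

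For treatment, the section on protocol deviations lists early stops of ceftriaxone that still count as treated per protocol. They include discharge, death, palliative care, a switch to another antibiotic for an infection, "an allergic reaction without anaphylaxis or a previous allergic reaction in medical history (see inclusion and exclusion criteria and protocol deviation in eligibility", and "other side effects of treatment". For the control arm the rule is: "In patients allocated to standard care, treatment was carried out according to the study protocol when patients did not receive preventive antibiotic therapy". Patients who cross over immediately are called protocol violations and stay in the ITT population.

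**The concern.** A safety table should answer what happened to the people who were given the drug. Here, entry to the table depends on whether the patient was eligible and was treated as allocated. Some patients who received ceftriaxone fail that test, and any reaction or serious adverse event they had goes with them. One group that fails is defined by allergy history, which bears directly on the Table 6 row for allergic reactions that led to stopping the drug.

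The trial gives a preventive antibiotic to patients without infection at admission, so the harm tables carry much of the benefit-risk judgement. Serious allergic events are few, and leaving out one or two can change what a reader sees.

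**Working it through.** There is no stated figure to reproduce. The check is to apply the SAP's rules to each kind of patient.

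| Patient | Rule that decides | In Tables 5 and 6? |
|---|---|---|
| Ceftriaxone arm, dosed, non-allergy eligibility deviation | Eligibility deviations are out of PP | No |
| Ceftriaxone arm, dosed despite a Table 1 allergy violation, not stopped because of that history | Same | No |
| As above, but stopped because the history surfaced | Early-stop list against eligibility rule | Unclear |
| Ceftriaxone arm, stopped for non-fatal anaphylaxis | Early-stop list | Unclear |
| Ceftriaxone arm, eligible, stopped because of fatal anaphylaxis | Death is on the early-stop list | Yes |
| Standard care, given preventive ceftriaxone | Treatment deviation | No |
| Ceftriaxone arm, never dosed because of immediate crossover | Treatment deviation | No |

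**The two unclear rows.**

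- *Allergy history surfaces.* The early-stop list seems to count this stop as treated per protocol. The patient still has an eligibility deviation, and the clause itself refers back to the eligibility criteria. Exclusion is the likelier result, but the text can be read as keeping the patient in.
- *Non-fatal anaphylaxis.* The list keeps allergic reactions only when there was no anaphylaxis, which suggests that anaphylaxis is handled differently. The same list then admits other side effects, and anaphylaxis to the study drug is a side effect. The reference to the eligibility criteria could also mean that the word concerns history.

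**Count.** Compared with counting everyone who received preventive ceftriaxone, the PP rules only remove such patients. The number of ceftriaxone reactions counted can therefore fall or stay the same, and cannot rise.

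**Percentage.** Inputs: 2,550 patients allocated 1:1 (SAP, summary of the study protocol), so 2,550/2 = 1,275 per arm. One case is 1/1,275 = 0.078 percentage points. Suppose m ceftriaxone-arm patients have an event, d of them are excluded, and k ceftriaxone-arm patients are excluded in all. The row changes from m/1,275 to (m − d)/(1,275 − k). It falls only if d/m > k/1,275, that is, if k < 1,275 × d/m. The documents give none of m, d and k. For illustration, with d = 1:

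- m = 5: the row falls only if k < 1,275 × 1/5 = 255.
- m = 10: only if k < 1,275 × 1/10 = 127.5.
- m = 20: only if k < 1,275 × 1/20 = 63.75.

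If d = 0, any exclusion raises the percentage. If nobody but the affected patient is removed (k = d = 1) and m = 10, the row goes from 10/1,275 = 0.78% to 9/1,274 = 0.71%.

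**Allergy violations alone.** Assume that e = 5 to 20 patients are dosed despite an excluded allergy and that a share r = 2% to 10% of them react. The expected number of missing reactions is e × r, from 5 × 0.02 = 0.1 to 20 × 0.10 = 2.0. The chance of at least one is 1 − (1 − r)^e, from 1 − 0.98^5 = 9.6% to 1 − 0.90^20 = 87.8%. This counts any reaction, whereas the Table 6 row counts only those that stopped the drug, so it overstates the loss from that row. It also treats every such patient as excluded.

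**The case against.** The best defence is that this is a mild form of per-protocol safety analysis. The early-stop list keeps deaths, non-anaphylactic allergy and other side effects, so the usual fault of dropping patients who stop because of harm is largely avoided. Eligibility violations are tabulated by arm in Table 1, in-hospital serious adverse events are reported to the trial office, and mortality is also a secondary outcome under the ITT main analysis. A reaction that stops ceftriaxone cannot occur in a standard-care patient who never receives it, so a few lost cases would not reverse the comparison in that row. The protocol, which is not shown, may settle the wording on anaphylaxis.

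Most of this stands and limits the consequences. It does not restore the missing patients: Table 1 counts violations but not what happened to those patients, and the safety tables name no second population.

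Three stronger readings are tempting, and the SAP does not support them:

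- *That patients stopped for anaphylaxis are excluded.* The clause is ambiguous, for the reasons given above.
- *That every patient with an excluded allergy is lost whatever the reading.* The clause on a previous allergic reaction leaves room to keep those stopped because the history surfaced.
- *That the reported percentage of allergic reactions is biased downward.* Only the count has a known direction. Removing never-dosed ceftriaxone patients shrinks the denominator and works the other way.

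**Conclusion.** The point holds in a limited form. The choice of the PP set for safety is explicit, and it removes at least two kinds of exposed patient: those dosed despite an eligibility deviation (with the one unclear exception) and standard-care patients given preventive ceftriaxone. How a stop for non-fatal anaphylaxis is classified is an unresolved ambiguity, not an established exclusion.

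The size is unknown and probably a few patients. The SAP gives no allergy, anaphylaxis or deviation rate, and every illustrative rate and count above other than the 1,275 per arm is an assumption. The primary outcome and mortality, analysed by ITT, are not affected. The change should be made because it is almost free and the tables concerned are the trial's main account of harm.

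**What to change.** In the section on the ITT and PP populations, replace the PP safety rule with analysis by treatment received. For Tables 5 and 6, compare all patients who received at least one dose of preventive ceftriaxone with those who received none, regardless of eligibility or reason for stopping. State that ceftriaxone given to treat a diagnosed infection does not move a standard-care patient to the ceftriaxone group. Keep the PP tables as supportive only.

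In the section on protocol deviations, state whether a stop for anaphylaxis, and a stop because an allergy history surfaced, are deviations for the PP analyses.

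The cost is SAP wording, since complications and serious adverse events are already recorded in the case record form. The drawback is that the safety arms no longer match the randomized groups exactly, so they must be labelled by treatment received. The PP set does not preserve the randomized groups either.
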